## Methods/Design

### Study design

Finding My Way (FMW) is a national level multi-site randomised controlled trial registered with the Australian and New Zealand Clinical Trials Registry with the registration number ACTRN12613000001796. Ethical approval to conduct the study has been sought and obtained from the Southern Adelaide Clinical, Royal Brisbane and Women’s and ACT Health Human Research Ethics Committees. Randomisation occurs at the patient level: patients are randomised to receive either the FMW intervention or an online attention-control. Procedural elements of this study follow CONSORT guidelines [32]. Attrition is monitored and reasons for non-participation and withdrawal are recorded in each arm. Data extraction and entry will be performed by research team members blinded to group allocation.

### Setting

Participation in the study occurs entirely online. The web-program is hosted by Flinders University (www.findingmyway.org.au), with Flinders University as the administering institution.

### Participants

#### Inclusion criteria

Patients are eligible to participate if they have been diagnosed with any cancer (e.g., breast, prostate, colorectal, testicular, lymphomas, haematologic or gynaecologic malignancies); their cancer is being treated with curative intent; they are currently receiving active cancer treatment (surgery, chemotherapy, radiotherapy), or, if they received surgery alone, have been diagnosed within the last six months; they are aged 18 years or over; and they have sufficient English language literacy to understand the information sheet and consent form and navigate the website, access to the internet (home or work), and an active email address and phone number.

#### Exclusion criteria

Patients are ineligible to participate if they have a diagnosis of advanced cancer.

#### Withdrawal criteria

Patients who opt to withdraw from the study are asked if they would consent to continue completing follow-up measures, and for any existing data to be included in analyses. If consent is not given, their data will be erased from the database along with any documentation related to their involvement.

#### Recruitment

An overview of recruitment and enrolment processes is provided in Figure 1. Participants are recruited from Australian hospitals and cancer centres according to any of the following methods:

**Figure 1 Fig1:**
[figure not shown]
Flow chart of study.

**Self-referral:** Participants self-refer to the website in response to advertisements placed in local and national newspapers, on websites or in newsletters of cancer agencies or support networks, or in waiting areas of cancer agencies and clinics of participating hospitals.**Direct approach:** Potential participants are approached directly by cancer clinicians or research assistants at participating hospitals, and are given a flyer containing a brief overview of the program and the website address. Verbal consent is obtained at this time for the research coordinator to provide either (i) a single reminder phone call, during which the research coordinator provides further information about the study and obtains the participants’ email address in order to send a direct link to the website, or (ii) when the patient cannot be contacted by phone, a single reminder letter providing further information about the study including the website address.**Letters of invitation:** Letters printed on the site’s letterhead and signed by the department head are sent to patients missed in clinic. These letters ask patients to consider participation and allow contact by the researchers (via an opt-out response slip). A single reminder phone call is then made to all patients invited to take part in the study if they do not respond to the invitation letter after two weeks. Protocol at some sites requires that a clinician/ research assistant from the recruiting hospital contacts the patient to obtain verbal consent for patient details to be provided, prior to contact by the research coordinator.

#### Enrolment

Participants follow the email link or type in the web address in order to access the website and register for the program. Registration generates an automatic email to the participant containing a link to activate their account. Following account activation, participants are directed to read an online information page and consent form. Eligibility criteria are clearly highlighted on the information page, and consent requires participants to check a box stating they do not have advanced cancer. Consent is obtained by the participant clicking on an “I agree” button on the online consent form.

Following the consent process, participants complete the baseline questionnaire. Participants are then randomised to either the intervention or attention-control condition and are directed to a welcome tutorial and their user home screen, from which they are able to access their first module immediately. Participants work through 6 modules: one new module is accessible each week, along with previously accessed modules. The order of module release is self-determined during a goal-setting exercise conducted when first logging into the program, which allows participants to identify which topics are most immediately relevant to them, and can be subsequently modified if certain topics become more relevant as participants progress through the program. Participants receive automated email reminders to use the program each week. A booster module, comprised of a summary of the key information points from the program and links back to topics and worksheets, is accessible one month later. The opportunity to provide qualitative and quantitative feedback is provided at the end of each module.

#### Randomisation

This study is a parallel RCT, with equal numbers of participants randomised to the intervention and control arms. Randomisation is automated within the website; the random allocation sequence is generated by a researcher blinded to the identity of participants using computer-generated random numbers, and allocation is then automated by the website in a 1:1 ratio. Randomisation is stratified by gender.

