### Analysis

#### Sample size

Longitudinal sample size calculation for repeated measures was conducted using a program developed by Hedeker [42]. Previous online interventions targeting distress in community samples have effect sizes ranging from .42 to .65 for depression, and from .29 to 1.74 for anxiety [19]. Therefore, a conservative small-to-moderate effect size was selected for the current study. Based on the pilot RCT findings, an attrition rate of 21% at each of the assessment points can be expected [29]. Thus for a study with 2 groups and 4 assessment points, power set at 0.80, statistical significance set at α = .05 (two tailed), total attrition set at 21%, an effect size set at 0.35 SD, and an expected primary endpoint standard deviation of 4.0 at each time point [43], 94 participants per group are required, summing to a total sample of 188 participants.

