#### Statistical analysis

Quantitative data will be analysed using the Statistical Package for the Social Sciences (SPSS) Version 17.0. Baseline differences between groups will be investigated using t-tests for continuous measures and *χ*^2^ tests of independence for categorical measures. Linear Mixed Effects Models (LMEM) will be employed to examine the efficacy of the intervention. The LMEM calculates a regression line for each individual while controlling for baseline observation (fixed main effects). Baseline observations will be entered as covariates to eliminate the influence of baseline variability, resulting in a 2 (group: intervention; control) X 3 (time: post-program; 3-month follow-up; 6 month follow-up) fixed effects model for each outcome variable, with random effects accounting for individual variation. This approach effectively equalises conditions at baseline and consequently allows for direct comparison between conditions at each follow-up point. In this context, (a) interactions between condition and time, (b) main effects of group and (c) post-hoc pairwise comparisons at each follow-up point are all indicators of intervention effects. This analysis offers the benefit of estimation maximisation; it provides joint modelling for each participant of observed and missing data based on maximising likelihood for population parameters as a function of the observed data. LMEM analyses are therefore robust with respect to handling missing data and unbalanced designs in longitudinal research as all participants with at least one observed *post-treatment* data point are included. That is, as baseline data is entered as a covariate, participants who do not complete any of the post-program assessments are not retained. To overcome this limitation and ensure this trial adopts a fully intention-to-treat design, multiple imputation will be performed for participants with only baseline-data. Therefore all participants, regardless of missing data at one or more assessment points, will be included in analyses and accurate parameter estimates obtained. Within-group effect sizes and reliable change indices will be calculated to provide a measure of the magnitude and clinical significance of changes respectively. To test for moderation, separate LMEM analyses will be conducted for each combination of moderator and outcome variable, where the moderator and group are entered in model 1 to control for main effects. The product term is then entered in model 2, to represent the interaction between group and moderating variable, and will indicate the moderating effect.

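### Gender is the stratification factor but is not a term in the stated efficacy model; adding it is a small, nearly free improvement

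*Protocol article*

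**What the plan says.** Under Randomisation, the article says that the sequence is generated "using computer-generated random numbers, and allocation is then automated by the website in a 1:1 ratio", and that "Randomisation is stratified by gender". The abstract repeats the stratification. No other stratification factor is named.

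Under Statistical analysis, the efficacy model is a linear mixed model. On covariates it says "Baseline observations will be entered as covariates to eliminate the influence of baseline variability". The fixed part crosses two groups with three follow-up times ("time: post-program; 3-month follow-up; 6 month follow-up) fixed effects model for each outcome variable"), and random effects cover the individual. Gender does not appear. In the moderator analyses, "the moderator and group are entered in model 1 to control for main effects", followed by their product; gender does not appear there either. The characteristics listed under Moderators of outcomes also omit gender, although it must be known before allocation for the stratification to work.

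**The concern.** When a trial balances its arms within levels of a factor that predicts the outcome, the treatment estimate varies less than it would under unrestricted allocation. A model without that factor leaves its effect in the residual variance. The model-based standard error is then larger than the true one, the test rejects less often than its nominal level, and some power is lost. The usual rule is therefore that the analysis follows the randomisation. Here the design uses one factor and the stated model does not use it.

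What is at stake is the width of the confidence intervals and a little power. Bias of the estimate and inflation of false positives are not at stake.

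**Working it through.** **Inputs from the article (Sample size, Randomisation):** 188 participants, 94 per group; two-sided 5% test; "power set at 0.80"; effect 0.35 SD; total attrition 21%; 1:1 allocation stratified by gender.

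**Inputs assumed:** R², the share of follow-up variance remaining after the baseline score that gender explains. The article gives no figure. The main range is 0.01 to 0.05, with 0 and 0.10 as outer values.

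**The plan's own figure.** At a single time point, n = 2(1.96 + 0.84)²/0.35² gives 129 per group, or 129/0.79 = 164 after attrition. The stated 94 therefore relies on the repeated measures. Averaging four time points with within-person correlation ρ, n = 2(1.96 + 0.84)²(1 + 3ρ)/(4 × 0.35²), divided by 0.79, gives 90 at ρ = 0.40 and 95 at ρ = 0.44. So 94 is reachable, but it cannot be confirmed because ρ is not stated. Gender enters none of these formulas, so the sample size does not depend on this point.

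**Case A: allocation balanced within gender, such as by blocks.** The true standard error is √(1 − R²) times the one reported without gender. Hence:

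- Reported over true standard error = 1/√(1 − R²)
- Actual type I error = 2[1 − Φ(1.96/√(1 − R²))]
- Power of the stated model = Φ(0.84/√(1 − R²)), where 0.84 = 2.80 − 1.96
- Power with gender added = Φ(2.80/√(1 − R²) − 1.96)

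Both power formulas are calibrated to 80% at R² = 0.

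| R² | SE too large by | Actual alpha | Power, stated model | Power, gender added |
|---|---|---|---|---|
| 0 | 0% | 0.0500 | 80.0% | 80.0% |
| 0.01 | 0.5% | 0.0489 | 80.1% | 80.4% |
| 0.05 | 2.6% | 0.0443 | 80.6% | 82.0% |
| 0.10 | 5.4% | 0.0388 | 81.3% | 84.0% |

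The gain is about 0.3 to 1.4 percentage points over the main range, and 2.7 at R² = 0.10.

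**Case B: simple randomisation within gender.** The true standard error is then not reduced by design, so the stated model's standard error is correct and its test keeps its level. Adding gender helps only as any prognostic covariate does: 80.0% against roughly 80.4% to 82.0% over the main range.

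**Simulation check.** This used analysis of covariance at one follow-up as a simplified stand-in for the mixed model: 148 completers (188 × 0.79), 3,000 replicates per scenario, 60% of one gender, R² = 0.10, no treatment effect.

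- Blocks of 4 within gender, no gender term: mean reported SE 0.165, empirical SD of the estimate 0.158, rejection 3.6%.
- Blocks of 4, gender added: 0.156 against 0.158, rejection 4.9%.
- Simple randomisation, no gender term: 0.165 against 0.164, rejection 4.8%.

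Under blocking, the empirical SD is 0.158 with or without gender. Only the reported standard error changes.

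**The case against.** The strongest reply is that the effect may be nil. It needs restricted allocation within gender, and the Randomisation section mentions no blocks. It also needs a gender effect left over after adjustment for the same outcome at baseline, and the article reports no such association. A link between gender and cancer type makes one plausible but does not show it. The article is also a condensed account, and a full analysis plan could add gender.

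Much of this stands. It makes the size conditional and small. It does not remove the mismatch, because the article sets out the model's terms and the stratification factor is not among them. Simple randomisation within each gender would achieve nothing that unstratified allocation does not, so balance within gender is the natural reading, though still an inference.

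A reader might go further in three ways that the article does not support:

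- *The standard errors are too large.* This holds only under both conditions above.
- *The precision gained by stratifying is thrown away.* The estimate keeps it; the reported uncertainty fails to show it.
- *The planned baseline tests will choose the covariates.* The article says "Baseline differences between groups will be investigated using t-tests for continuous measures" and plans chi-square tests for categorical measures, but nowhere says that the results decide what enters the model. Whether to run such tests is a separate reporting matter and adds nothing to this point.

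**Conclusion.** The point holds as a minor mismatch between design and analysis. If allocation is balanced within gender and gender explains 1% to 5% of the residual variance (an assumed range), the stated model gives standard errors 0.5% to 2.6% too large and a test at 4.9% to 4.4%. It gives up about 0.3 to 1.4 percentage points of power. With no residual gender effect nothing is lost. With unrestricted allocation there is no bias in the standard error, only a forgone covariate gain of similar size. In every case the estimate is unbiased, any error is on the conservative side, and 188 participants remains the planned number.

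**What to change.** Add gender as a prespecified fixed effect in the linear mixed models for the primary and secondary outcomes, alongside the baseline score. Carry it into the multiple imputation model and both steps of the moderator models, so that all analyses rest on the same covariates. If there is a reason to leave gender out, state it.

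The cost is one term and one degree of freedom per model, with no new data collection. The change is right whether or not allocation is blocked within gender, so it need not wait for that detail. Fixing it before unblinded analysis also removes any later choice between adjusted and unadjusted results.

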#### Blinding

Participants are blinded to their intervention assignment; while they are aware there are two different versions of the website (explained as ‘information’ and ‘activities’ versions), they are not informed that one is a ‘control’ condition, are not aware which is the primary intervention being evaluated, and are blinded as to their own treatment group allocation. A list of blinded participant details is accessible to the research assistant for the purposes of conducting reminders about follow-up surveys.

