**Methods/Design:**

The study is a multi-site Randomised Controlled Trial (RCT) seeking to enrol 188 participants who will be randomised to either the *Finding My Way* Intervention or an attention-control condition. Both conditions are delivered online; with 6 modules released once per week, and an additional booster module released one month after program-completion. Participants complete online questionnaires on 4 occasions: at baseline (immediately prior to accessing the modules); post-treatment (immediately after program-completion); then three and six months later. Primary outcomes are general distress and cancer-specific distress, with secondary outcomes including Health-Related Quality of Life (HRQoL), coping, health service utilisation, intervention adherence, and user satisfaction. A range of baseline measures will be assessed as potential moderators of outcomes. Eligible participants are individuals recently diagnosed with any type of cancer, being treated with curative intent, aged over 18 years with sufficient English language literacy, internet access and an active email account and phone number. Participants are blinded to treatment group allocation. Randomisation is computer generated and stratified by gender.

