### Intervention and control arms

#### Intervention

*Finding My Way* is a 6-week password-protected CBT internet application comprised of three main components: (1) psycho-education, (2) cognitive-behavioural worksheets/strategies including worksheets, quizzes, relaxation and meditation exercises, and (3) survivor testimonials. Each week a new module is released to participants, and participants can continue referring back to previous modules throughout the study.

The 6 modules address: (i) starting treatment – working with your medical team, covering assertive communication and decision making, (ii) coping with physical symptoms and side effects – including fatigue, pain, insomnia, and provides activity pacing worksheets, and relaxation audiotracks; (iii) coping with emotional distress – which covers depression, anxiety, anger and stress, and provides cognitive restructuring diaries, and mindfulness audio-tracks; (iv) body image, identity and sexuality – with psychosexual worksheets, and therapeutic writing activities; (v) your family and friends – comprising further assertive communication and needs assessment worksheets; and (vi) completing treatment, which includes self-management strategies to facilitate healthy lifestyles.

A private online note-taking feature, mood monitoring/management, and a resource section with links to reputable cancer-related organisations and other health websites are also available throughout the duration of the program. The program is outlined in Table 1.

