#### Attention control

An information-only version of *Finding My Way,* developed to provide an appropriate attention control for the study, covers the same 6 module topics without any of the worksheets, activities, relaxation exercises, or note-taking feature. Our previous research indicates that an attention control condition does not significantly reduce distress [29], and provides a more rigorous test of the intervention.

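### The protocol claims participants are blinded to their own allocation, but the labels they are given name the visible difference between the arms; only the study hypothesis can be masked

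*Protocol article*

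**What the plan says.** The Abstract (Methods/Design) states: "Participants are blinded to treatment group allocation". The Blinding section gives the detail, in three parts.

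- **Told to participants:** "while they are aware there are two different versions of the website", these being "explained as ‘information’ and ‘activities’ versions".
- **Withheld from participants:** "they are not informed that one is a ‘control’ condition".
- **Property claimed as a result:** they "are not aware which is the primary intervention being evaluated, and are blinded as to their own treatment group allocation".

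The Intervention section lists among the program's main components "cognitive-behavioural worksheets/strategies including worksheets, quizzes, relaxation and meditation exercises". The Attention control section describes an information-only site that "covers the same 6 module topics without any of the worksheets, activities, relaxation exercises, or note-taking feature".

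The Outcomes section says that primary, secondary and moderator outcomes are collected by online self-report. The two primary measures, the DASS-21 total and the 17-item post-traumatic stress scale, are both questionnaires of this kind. The Study design section adds that the staff who extract and enter data are blinded to group.

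**The concern.** Masking of allocation and masking of the hypothesis are different properties. Under the first, a participant cannot tell which version they received. Under the second, they may know the version but not its role in the trial. The Blinding section claims both, and the Abstract keeps only the stronger one.

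The labels disclosed to participants describe the arms by the feature that separates them. Someone who knows that an activities version and an information version exist, and then works through one of them, has what they need to recognise their own.

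What is at stake is the reading of the primary result. Participants score their own distress. If they know their version and hold expectations about it, those expectations can enter the scores. A reader or risk-of-bias assessor who relies on the Abstract would take this route to be closed when it is not.

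**Working it through.** The point is one of internal consistency. The protocol gives no figure to reproduce and no arithmetic applies. The check sets the relevant sections side by side.

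1. **What participants know beforehand (Blinding).** There are two versions, labelled information and activities. They are not told that either is a control.

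2. **What each arm sees (Intervention, Table 1, Attention control).** Table 1 lists worksheets or activities for each of the six modules, and links back to worksheets for the booster. The control covers the same six topics "without any of the worksheets, activities, relaxation exercises, or note-taking feature". The labels in step 1 therefore describe the content difference between the arms.

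3. **Whether anything hides the difference.** The article describes no feature that would do so. The Enrolment section mentions a goal-setting exercise at first login without separating the arms. The features listed as removed from the control do not include survivor testimonials or mood monitoring. The sites may thus look alike at the start, and recognition may come only as modules are used. The post-treatment questionnaire follows the sixth module, seven weeks after baseline, which leaves time for recognition among those who use the program.

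4. **What remains masked.** Knowing the version is not knowing its role. The first two claims in the Blinding section (not told that one is a control, not aware which is being evaluated) are compatible with steps 1 to 3. The third, blinding to own allocation, is not.

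5. **Who assesses the outcome (Outcomes, Primary outcome).** The participant does, for both primary measures. Blinded extraction and entry act after the participant has given the answer, so they cannot remove an expectancy effect from it.

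6. **Whether the analysis removes it (Outcomes, Statistical analysis).** Baseline is completed before randomisation and entered as a covariate. That adjusts for differences present before allocation. An expectancy effect arises afterwards and would enter the group contrasts at post-program, 3 months and 6 months.

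**The case against.** The strongest reply is that the Blinding section hides nothing. It states the labels and what is withheld, so a careful reader can see that the masking concerns the hypothesis. Full participant blinding is rarely achievable when the intervention consists of visible activities. The design also takes sensible steps: a topic-matched control on the same platform, automated allocation, undisclosed control status and blinded data handling. All of this is true, and it makes the point one of wording and interpretation rather than a hidden design flaw. It does not make the allocation claim correct, and the Abstract carries that claim without the explanation.

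A reader might also infer more than the documents support.

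- **That everyone knows their arm at first use.** Each participant sees one site only, and the article does not document how quickly or how widely people recognise their version. Probable recognition by those who use the modules is as far as the text goes.
- **That all outcomes are self-reported.** Website use is logged automatically, and the Abstract lists adherence as a secondary outcome. Self-report holds for both primary outcomes, which is what matters here.
- **That the bias favours the intervention.** Nothing shows that participants regard information as the lesser version. Higher control dropout is equally speculative, since worksheets add burden and could raise dropout in the intervention arm. Attrition and withdrawal reasons are recorded by arm.
- **That the bias has a known size.** One could assume a shift of 0.05 to 0.15 SD and set it against the 0.35 SD planning effect: 0.05/0.35 = 14% and 0.15/0.35 = 43%. Those percentages only restate the assumption, because no section supplies a shift.

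**Conclusion.** The claim of blinding to own allocation is wrong as written in the Abstract and the Blinding section. The design described can mask which version is the control or under test. It cannot be relied on to mask which version a participant received.

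The consequence is possible expectancy bias in two self-reported primary outcomes, of unknown size and direction. The comparison remains randomised and analysable. What changes is how far the trial may claim that its primary result is protected from participants' expectations.

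The conclusion assumes that participants are given the labels as the Blinding section reports them, that the sites differ as the Intervention and Attention control sections describe, and that participants use enough of the modules to notice. It depends on no assumed bias figure.

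**What to change.** In the Abstract, the Blinding section and the trial report, replace the claim of blinding to allocation with wording such as: participants are masked to the study hypothesis (not told which version is the control), not to the content of the version received. State possible expectancy bias as a limit on conclusions about the self-reported primary outcomes. This needs only a text change; the downside is a weaker blinding claim.

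Optionally, add one post-treatment item asking which version participants believed was under test, and report it by arm. It would describe how far hypothesis masking held. Because it is asked after use, answers may reflect benefit experienced, so it should not be used to correct the treatment effect.

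Removing the labels from participant-facing text is not part of this fix. Participants would still see their own content, so it would not create allocation blinding. It would also make the consent information less descriptive and, if enrolment has begun, would give earlier and later participants different information.
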